# Background

Emotion dysregulation among children can frequently be observed in different contexts, interfering with various important aspects of life, including general development, social skills, and family dynamic in the home. The following paragraphs introduce the concept of emotion regulation, and explore the link of emotion dysregulation to other issues such as irritability, stress, inattention, and hyperactivity/impulsivity. Further, the increasing role of vitamins and minerals as an intervention for emotion dysregulation and irritability is discussed by means of research from the past decade, illustrating the relevance of nutritional research as a treatment option. Lastly, the aims and objectives of the proposed study are presented.

Competent emotion regulation is defined as the “extrinsic and intrinsic processes that serve to monitor, evaluate, and modify emotional reactions” (Thompson, 1994, p. 27-28), referring to the effective management of behaviours following experiences in the environment that trigger emotions. Competent emotion regulation does not only foster empathy but also enables one to know the difference between internal emotional experiences and the external expression of emotions, behave socially appropriate (Thompson, 2019), and adapt to external stressors by identifying, understanding, and integrating emotional information (Garnefski et al., 2007; Saarni, 1984; Terwogt & Stegge, 1995; Thompson, 1994). It is a complex concept that depends on multiple aspects, including the person’s developmental status, subjective perceptions, cultural norms and values, and past experiences (Kopp, 1982; Saarni, Campos, Camras, & Witherington, 2007). When children are five, they are usually competent to appropriately regulate their emotions and behaviour (Carlson & Wang, 2007), and this has a positive impact on various developmental factors such as social skills, language, and cognitive abilities (Kamphaus, 1987). For example, in preschool children, competent emotion regulation has been associated with superior social behaviour, social competence, and abilities to adjust to the environment, as well as being liked by peers and teachers (Denham et al., 2003).

Because competent emotion regulation helps us to effectively face challenges, adequate emotion regulation skills are required for successful coping with stressful situations or life events (Saarni et al., 2007; Wong et al., 2006), which might be a reason why emotion regulation is frequently associated with stress. The overlap between emotion regulation and stress might also be explained by common physiological mechanisms, as they both involve activation of the hypothalamic–pituitary–adrenal (HPA) axis (Wang & Saudino, 2011). Specifically, Zimmermann and Stansbury (2004) showed that competent emotion regulation acts as a predictor for lower levels of cortisol, a stress hormone, which is initiated by triggering the HPA axis. In addition, evidence suggests that the prefrontal cortex is activated both during stress and emotion regulation processing (Beauregard, Lévesque, & Bourgouin, 2001; Ochsner, Bunge, Gross, & Gabrieli, 2002), indicating that there is a neuroanatomical overlap in the brain areas linked to both states.

Whereas competent emotion regulation has many beneficial outcomes, emotion dysregulation is associated with a series of adverse effects, including psychosocial issues, anxiety, poor academic achievement, and behavioural escalations in the home (Zeman, Cassano, Perry-Parrish, & Stegall, 2006). Emotion dysregulation is operationally defined as “a pattern of emotional experience and/or expression that interferes with appropriate goal-directed behaviour” (Beauchaine, 2015, p. 876), with goal directed behaviour referring to competent emotion regulation and its associated functions as described above (Thompson, 2019). In contrast to competent emotion regulation, it is the maladaptive management of emotional responses, and has been shown to damage social relationships and can possibly lead to isolation and psychosocial stress (Eisenberg et al., 1993; Stansbury & Gunnar, 1994). These negative outcomes are highlighted by the longitudinal Dunedin cohort study, which revealed that children with uncontrolled temperament at age 3 were twice as likely to develop a gambling disorder at age 21 and 32 relative to children classified as having a well-adjusted temperament (Slutske et al., 2021). The same study showed that better self-control skills in children predicted improved physical health, reduced substance use disorders, and less criminal offending in later life (Moffitt et al., 2014).

Emotion dysregulation is a highly prevalent phenomenon, particularly in children and young people, and frequently linked to psychiatric disorders (Pylypow et al., 2020). In healthy youth, prevalence rates range from 3% to 20% (Brotman et al., 2006), which increase up to 33% in individuals with psychiatric conditions (Stringaris, 2011). Further, it is increasingly acknowledged as a prominent feature of Attention-Deficit/Hyperactivity Disorder (ADHD) (Retz, Stieglitz, Corbisiero, Retz-Junginger, & Rösler, 2012), a common psychiatric disorder characterized by problems with hyperactivity/impulsivity and inattention (American Psychiatric Association, 2013). Depending on comorbid diagnoses, up to 90% of children with ADHD also struggle with emotion dysregulation (Mick, 2005). Similar to emotion dysregulation, ADHD is linked to adverse long-term consequences, such as poor academic performance, impaired social relationships, and increased substance abuse (Barkley, 2006).

Although emotion dysregulation is common, it is frequently examined within various psychiatric disorders rather than as an independent construct, possibly impacting the establishment of treatment strategies (Brotman et al., 2017). So far, treatment for emotion regulation has included psychopharmacologic medication; particularly, in one placebo-controlled RCT, the selective serotonin reuptake inhibitor (SSRI) fluoxetine improved aggression and irritability in adults relative to a placebo (Coccaro et al., 2009). In another placebo-controlled RCT with youth with severe and chronic irritability, a higher response-to-treatment-rate was seen in the participants who received an SSRI in combination with a stimulant (citalopram and methylphenidate) compared to a placebo combined with a stimulant only (methylphenidate) (Towbin et al., 2020); however, the overall response rates were modest (35% and 6% respectively).

Psychiatric medication in the form of stimulants are often prescribed as the main form of treatment for individuals with ADHD, who frequently have problems with emotion dysregulation (Barbaresi et al., 2014). However, although research has shown that stimulant medications are an effective intervention in the short term (Biederman et al., 2004), issues have been raised regarding their long-term benefits (Advokat, 2010, Currie et al., 2014; Molina et al., 2009). Additionally, the literature shows that while stimulant medication may benefit some ADHD-related symptoms, it frequently fails to improve emotion dysregulation (Shaw et al., 2014; Posner et al., 2014), particularly in younger people (Posner et al., 2014), indicating that emotion dysregulation might be a separate construct to ADHD. In addition, several concerning side effects have been observed with stimulant medication including weight reduction and suppression of growth (Thomas et al., 2013), effects on brain development depending on the age when the stimulants are used (Andersen, 2005), nausea, cardiovascular issues, insomnia, and agitated behaviours (Baumgaertel, 1999). Overall, the current evidence on psychiatric medication as a treatment for emotion regulation in youth is sparse and suggests limited benefits, posing a need to future research in this area (Towbin et al., 2020; Brotman et al., 2017).

Alternatively, behavioural interventions, particularly Cognitive Behavioural Therapy (CBT), have shown to be an effective intervention for young individuals who have issues with anger and aggression (Brotman et al., 2017). CBT helps such children learn how to minimize maladaptive behaviour by considering alternative and adaptive ways to think about and react to triggering situations (Kazdin, 2010). However, although behavioural therapies for young people are frequently suggested, there is a lack of guidelines on how to apply evidence-based treatment strategies (Daley et al., 2018) and a shortage of trained clinicians and specialist services (Miller et al., 2014), which can interfere with effective treatment delivery.

Due to some of the downsides of the current treatment options as well as the fact that dysregulation of emotions is difficult to treat and does not appear to respond as well to some of the current treatment options, other treatments have been investigated. In particular, there has been an increase in investigations of the role of nutrition in mental health, and evidence has established that the intake of healthy food, such as fruit, vegetables, legumes, and healthy fats, is linked to improved mental wellbeing (Jacka et al., 2017; Parletta et al., 2018). However, given the research that has uncovered that the nutrient density of our foods and our soils has been progressively decreasing (Rucklidge & Kaplan, 2021), and may become more so, as a consequence of climate change (FAO, 2017), eating foods that are considered nutritionally dense might no longer have the desired beneficial effects on our mental health, making it important to seek alternative ways of increasing nutrient availability in our brain. Supplementing food consumption with nutrients might be one way to do so, and over the past decades, there has been an increasing number of studies investigating the role of consuming additional nutrients in the form of nutritional supplements on mental wellbeing.

Initially, researchers investigated single rather than multinutrient interventions in the context of mental health issues; however, due to overall disappointing results, the focus is increasingly on combined nutrient treatments, including broad-spectrum multinutrient supplements that contain the full array of essential vitamins, minerals, and amino acids. Reasons for this shift include the fact that people tend to have multiple nutrient deficiencies rather than just one, and the evidence shows that multiple nutrient deficiencies are highly prevalent across the globe, with approximately two billion people experiencing some form of deficiency (Bailey et al., 2015). In fact, treating deficiencies with a single supplement can have adverse effects, as it can lead to imbalances in other nutrients (Mertz, 1994). Further, vitamins and minerals do not exert their effects on the brain separately but work together with other vitamins, minerals, and amino acids, challenging the initial ‘one disease-one nutrient’ approach (Mertz, 1994).

To date, various theories have been developed that aim to explain how micronutrients exert their positive effects on psychiatric symptoms. Firstly, micronutrients are an essential cornerstone of the synthesis of some of the neurotransmitters that are involved in mood, such as dopamine and serotonin, particularly, vitamin B9 (folate), B12, and B6, as well as the minerals iron, copper, and molybdenum (Stough et al., 2011). Specifically, creation of dopamine and serotonin involves multiple metabolic processes that utilize enzymes and co-enzymes that require various vitamins and minerals as cofactors. If vitamins and minerals are not available, enzymes and co-enzymes cannot function properly, impairing dopamine and serotonin production and potentially interfering with mental wellbeing (Rucklidge & Kaplan, 2013).

Further, micronutrients are essential for the functioning of the mitochondria, the power plants for neurons and glia, that are crucial for various physiological processes for brain functioning, including energy production, metabolic processes, and neuronal communication (Stough et al., 2011). Evidence suggests that impaired mitochondrial functioning might be involved in bipolar disorder, ADHD, and Autism Spectrum Disorder (Rossignol & Frye, 2012; Russel et al., 2006; Young, 2007), and although it is not yet well established, vitamin A, C, and K might support mitochondrial functioning, supporting optimal brain functioning (Rucklidge & Kaplan, 2013).

These beneficial effects are underlined by recent evidence, illustrating the positive effect of broad-spectrum micronutrients on a variety of mental conditions and psychological symptoms, including emotion dysregulation and irritability (Rucklidge et al., 2019; Rucklidge et al., 2014; Julia & Kaplan, 2013). For instance, Rucklidge et al. (2018) conducted a double-blinded RCT with 93 7-to-12-year-old children with ADHD, with some children having severe problems with emotional dysregulation and aggression. A clinician rating of global functioning (based on consideration of parent, teacher and child reports) showed that nearly double the number of children in the micronutrient group were identified to be ‘much’ to ‘very much’ improved relative to the placebo group (47% versus 28%). In comparison with the placebo group, children who took the micronutrients showed a greater improvement in aggression (*d* = 0.52), emotionally dysregulated behaviour (*d* = 0.66), dysregulated mood (*d* = 0.35), conduct problems (*d* = 0.48), and problem behaviour based on the parent- (*d* = 0.41) and teacher-rated (*d* = 0.45) questionnaires, although it is important to note that not all the group differences were statistically significant.

Further, in an open label, on-off-on-off (reversal design) study, 14 children with a diagnosis of ADHD between 8 and 12 years old were assessed over a period of 6 months. In particular, children were given micronutrients for 8 weeks, then the treatment was withdrawn for 4 weeks, then reintroduced for 8 weeks, and withdrawn again for 4 weeks (Gordon et al., 2015). In the treatment phases, participants showed a large and statistically significant improvement across a variety of symptoms, including issues with social behaviour and conduct problems, which are symptoms frequently related to emotion dysregulation. In addition, over two-thirds of the participants were identified as ‘much’ or ‘very much’ improved after the second treatment phase. This beneficial effect was reversed when the treatment was withdrawn, which illustrates the potential benefits of micronutrients on behavioural regulation.

To illustrate the importance of nutrition in psychiatric symptoms not only in children but also adults, in an open-label pilot study, 14 adults between the age of 28 and 55 with diagnoses of both severe mood dysregulation and ADHD were given micronutrients for 8 weeks (J. Rucklidge, Taylor, & Whitehead, 2011). Data revealed that the participants experienced moderate to large statistically and clinically significant benefits across emotional symptoms, such as mood, mania, emotional lability, as well as hyperactivity/impulsivity and inattention (*d* = 0.66-1.96). These findings illustrate that micronutrients may represent an alternative treatment path for those who struggle with emotion dysregulation and irritability that needs to further be explored.

As mentioned above, emotion regulation/emotion dysregulation is frequently associated with stress, and stress is linked to various adverse effects, including the development of cardiovascular disease, atherosclerosis, oxidative stress, and inflammatory reactivity (Huang, Webb, Zourdos, & Acevedo, 2013), as well as poorer mental wellbeing, and academic underachievement (Myers et al., 2012). As an attempt to reduce stress as well as trial a new delivery modality for the micronutrients, an unpublished randomized, double-blinded trial conducted in Te Puna Toiora investigated the effect of this delivery modality on stress and mental wellbeing in UC students. The product tested was powdered multinutrient straws called EMPowerplus Lightning Stiks^TM^, which use Direct-to-Mouth technology in which the multinutrients are absorbed through the tissues of the mouth. This different modality means that the dose of the micronutirents is much lower than has been previously used in other research on broad spectrum micronutrients. Indeed, all doses are well below the recommended Dietary Allowance (RDA) and none are given in a dose above the Upper Limit (UL). None of the doses are given at a medicinal level. The Lightning Stiks^TM^ consist of a blend of 36 ingredients, including vitamins, minerals and amino acids, called EMPowerplus, and previous research has shown that this formula (taken in capsules) can improve stress, anxiety, and mood in adults as well as in children (J. J. Rucklidge et al., 2012; J. J. Rucklidge & Blampied, 2011; Sole, Rucklidge, & Blampied, 2017; Stough et al., 2011). Preliminary data analysis of this trial (STAR trial - not yet published) revealed that the Lightning Stiks^TM^ reduced stress in students more rapidly relative to the placebo group, although the group difference was not statistically significant (*d* = 0.39, *p* = .108). Additionally, the multinutrient group displayed a greater beneficial impact on emotion regulation and irritability compared to the placebo group (*d* = 0.54, *p* = .024), as well as reduced symptoms of anger (*d* = 0.62, *d* = .011).

Irritable children who struggle with emotion dysregulation, anger management, and stress coping can be found across all ages and display issues well-known to mental health practitioners and psychologists; as such, addressing the problems displayed by these children is important in future research. Anecdotal reports suggest that the effects of the Lightning Stiks^TM^ are similar to the capsule version, with many users reporting feeling calmer, happier, and more focused. Additionally, and aligning with the findings of the STAR trial, anecdotal reports of children in the community who have taken them suggested that the nutrients were well tolerated with reports of improvement in emotion dysregulation in some of the children, showing that the Lightning Stiks might be a suitable treatment for emotion dysregulation in children.

One recent study study within Te Puna Toiora researched the impact of micronutrients on children with traumatic brain injury, and for these children, taking the micronutrients (as capsules or powder) was a major struggle due to the unpleasant taste and smell. In addition, children frequently struggle with swallowing numerous capsules; a study in 2008 found that 30%-40% of parents had children (aged 0-26 years) who had difficulties with swallowing a standard sized pill, and more than 50% were unable to swallow it at all (Polaha et al., 2008). These findings underline that the Lightning Stiks^TM^ might be a new, more convenient way for children to take micronutrients.

Further, as mentioned, safety concerns associated with the doses of the micronutrients present in the Lightning Stiks^TM^ are unlikely because the nutrient doses of each ingredient are below the RDA. This low risk is supported by the findings of the STAR trial (not yet published), showing that only a small number of side effects were present in the study (drowsiness and reduced appetite), and these were temporary and disappeared during the duration of the trial. Finally, by improving emotion regulation skills, stress coping mechanisms might be improved as well, minimising the negative impact of stress on the individual.

Overall, evidence suggests that micronutrients may have a beneficial effect on emotion dysregulation, irritability, and stress. Given that emotion dysregulation in children is a common phenomenon which does not only affect the child but also the family, teachers, and social relationships, it is an issue that needs to be addressed in future research. Current treatments for emotion dysregulation show limitations in efficacy and implementation, and as such, future research needs to establish feasible and easy-to-implement interventions that can be put in place. Nutritional interventions present as non-invasive and have a low incidence of side effects that are usually mild and temporary. Further, because the Lightning Stiks^TM^ are available in multiple flavours and do not have the usual unpleasant taste and smell that multinutrient pills have, they might be a convenient alternative treatment for children, representing the foundation for the proposed study.

## Aims and Objectives

The proposed study aims to investigate whether the Lightning Stiks^TM^ are an effective short- and long-term treatment for children between 5 and 10 years of age who struggle with emotion dysregulation and irritability. It will be the first independent explorative study to investigate the feasibility and effectiveness of the Lightning Stiks^TM^ as an intervention for children with emotion dysregulation.

**Hypotheses:**

1. The Lighting Stiks^TM^ will be found to be an acceptable and effective intervention to reduce irritability, behavioural- and emotional dysregulation in 5-10 year-old children.

2. The beneficial effect of the micronutrients will be present during the phases where participants take the micronutrients, and diminish during phases where the treatment is withdrawn.

3. There will be differences in the first month between the two groups in emotion dysregulation when group 1 will be taking the nutrients and group 2 will not (see design), with group 1 showing better emotion regulation than group 2.

4. There will be differences in the second month between the two groups in emotion dysregulation when group 2 will be taking the micronutrients and group 1 will not, with group 2 showing better emotion regulation than group 1.

5. There will be differences in the third month between the groups in emotion dysregulation when group 1 will be taking the micronutrients and group 2 will not, with group 1 representing better emotion regulation than group 2.

6. During the final eight weeks of the trial, when both groups will take the nutrients simultaneously, both groups will display similar competencies in emotion regulation.

7. It is expected that the improved behaviour in children will reduce the parents’ symptoms of stress, potentially having an additional beneficial effect on the children’s behaviour.

8. The Lightning Stiks^TM^ will be found to be a safe intervention that has a low incidence of side effects which will be mild in severity and only last temporarily, and yields high consumer satisfaction in the participants.

9. The longer the participants take the Lightning Stiks^TM^ continuously at a time, the greater the beneficial effect on emotion dysregulation.

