# Method

## Study design

The proposed study will use a two-arm withdrawal open-label design, following the advice of Hersen and Barlow (1976) on how to evaluate the effect of drug interventions on behaviour using a single-case approach. In particular, the study will have two groups, and participants will be randomized in equal numbers to either group 1 or group 2 by means of a randomized block procedure.

There will be five study phases:

1. Study period 1: Online screening and baseline assessment: Participant children will be screened for eligibility (see below) by providing information regarding their demographics as well as completing measures assessing emotion dysregulation and irritability. If they are eligible, they and their parent(s) will meet with the study coordinator [name] at Te Puna Toiora during the week before the intervention period starts. During that meeting, eligibility will be checked, questions about the research answered, consent obtained, and the participant will complete a baseline assessment. In case the participants cannot be met in person (e.g., due to COVID-19 or because they live outside of Christchurch), meetings will be held and consent conducted over the phone or online (via Skype/Facetime/Whatsapp/Zoom). Consent forms can be uploaded and emailed/mailed back to Te Puna Toiora. Once consent is given, baseline data will be collected by means of an online survey (Qualtrics) including various psychometric measures (see below). Participants in group 1 will be given one month’s supply of Lightning Stiks^TM^ immediately after the baseline assessment. If participants cannot be seen face-to-face, the Lightning Stiks^TM^ will be delivered by courier. Those randomised to group 2 will have a delayed 4 week start (see Figure 1)
2. Study period 2: Group 1 will start taking the intervention for 4 weeks (ON-phase). Every two weeks, the parents will fill out various psychometric questionnaires assessing their children’s emotion dysregulation and irritability (see measures below), other symptoms linked to ADHD, sleep, diet, mood, anxiety and stress. Group 2 will be in a delayed baseline phase during study period 1, but will be monitored by answering the same psychometric questionnaires as group 1 every two weeks.

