3. Study period 3: The intervention in group 1 will be withdrawn for four weeks (OFF-phase), whereas group 2 starts taking the Lightning Stiks^TM^ (ON-phase). Both groups answer the same questionnaires as before every two weeks.
4. Study period 4: Group 2 stops taking the interventions (OFF-phase) whereas group 1 starts taking them for another 12 weeks (ON-phase). Both groups answer the same questionnaires as before every two weeks.
5. Study period 5: When Group 1 has been taking the Lightning Stiks^TM^ for four weeks, Group 2 starts taking the multinutrient intervention for another 12 weeks and will answer questionnaires every two weeks.

Every four weeks, the children’s parents and children will meet with the study coordinator at *Te Puna Toiora* to complete various psychometric questionnaires assessing their children’s behaviour, including hyperactivity/impulsivity, inattention, emotion dysregulation, irritability, sleep, social relationships, diet, and side effects. If participants cannot be met in person, the meeting will be held via Zoom. Both the child and the parent will answer the questions of the Measure it Yourself Medical Outcome Profile (MYMOP) (see below) jointly; otherwise, they will answer the questionnaires on their children’s or their own behalf. In addition, questionnaires assessing emotion dysregulation and irritability will also be emailed to another adult who is close to the child, such as a grandparent, aunts/uncles, or teachers, twice over the period whole study period. Please find a diagram with all study phases below.

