#### **Participant recruitment**

Participants will be recruited nationally across New Zealand, mainly by self-referrals following online advertisement on social media. Specifically, recruitment will take place through advertisement on Facebook (via the Mental Health and Nutrition Research Lab Te Puna Toiora account, the University of Canterbury Student Association (USCA) noticeboard), and Instagram (via the Te Puna Toiora account). Further, advertisement posters and brochures will be distributed around the UC campus, with local General Practitioners and mental health service providers. To increase Māori participation in the study, efforts will be made to engage with Māori service providers.

*Sample size*

Forty participants will be sought for the study, split 20:20 between group 1 and 2 . This number of participants is considered a sufficient sample size to determine whether the Lightning Stiks^TM^ are successful in reducing emotion dysregulation with sufficient power. This is a reasonable expectation as it allows for an adequate number of successful replications between participants, following the What Works Clearinghouse Standards for single-case designs (Handbook, n.d.).

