*Abbreviated Acceptability Rating Profile (AARP) (Tarnowski & Simonian, 1992).* At the end of the trial, parents will be asked whether they perceive the Lightning Stiks^TM^ as a helpful and acceptable treatment to reduce the children’s irritability and emotional dysregulation by means of the AARP. The AARP is a parent-administered, 8 item rating-scale, with each item being scored on 6-point Likert scale (1 = ’strongly disagree’ to 6 = ‘strongly agree’) asking about the child’s treatment acceptability, likeability, effectiveness, and helpfulness of the intervention. The AARP has shown to have excellent internal consistency (*α =* .95-.98) and adequate discriminant validity (Tarnowski & Simonian, 1992).

*The Depression Anxiety and Stress Scale-21 (DASS-21):* The DASS-21 is the shorter, 21-item of the original 42-item DASS-42 (Lovibond and Lovibond, 1995). It is a publicly available questionnaire, which assesses an individual’s symptom severity associated with depression, anxiety and stress using a 0 – 3 Likert scale. Cut-offs have been provided to indicate normal, mild, moderate, severe, or extremely severe problems; anything below 10 (for depression), 8 (for anxiety) and 15 (for stress) is considered within the normal to mild range. The scale has excellent reliability (*ICC* = .93) as well as a sufficient construct validity (Henry & Crawford, 2005). In the proposed study, it is completed by the parents to measure their own’s wellbeing and stress every four weeks.

*The Side-Effect Checklist (revised) (ASEC) (Uher et al., 2009):* The ASEC will assess side effects, safety and adverse events of the intervention. The ASEC has been adapted for the purposes of this study to remove references to anti-depressants. In addition, the item regarding sexual dysfunction is removed since it is not applicable for children, and the potential adverse event ‘rash’ was added because this has been a common side effect in past studies. Side effects will be assessed every two weeks, and any concerning adverse events will be discussed with the study physician and the co-investigators. In the case of a serious adverse event, the investigators will consider whether termination of the study is necessary.

*Parent- and child administered*

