Research participants will be informed if any new information regarding the products' safety is brought to our attention during the trial. If we find that a child’s symptoms have increased to a clinically significant degree or that the product is causing any harm, we may discuss with the participant and their family the possibility of withdrawing them from the trial or may decide that they should discontinue their participation in the trial. Participants may be referred to their General Practitioner until the condition associated with an adverse event has resolved or until it is stable. All adverse events will be documented. Serious adverse events would include events that result in hospitalisation, life-threatening disability or death.

If a participant, for any reason, requires treatment with certain therapeutic agents (i.e. antibiotics), we will note what they are taking and for how long. If a protocol exclusion violation has occurred (i.e., participant requires psychiatric medications), the participant’s involvement will be discontinued. If any participant is discontinued from the trial or decides to withdraw, we will carry out follow-ups to confirm the well-being of participants.

Potential side effects

As mentioned previously, anecdotal reports have reported that as a consequence of taking the Lightning Stiks, individuals may suffered from headaches in the first few days of taking them. However, this could potentially be minimized by taking only half a Stik initially, and increasing the dose over 2 days. Further, the doses of the ingredients are much lower than those found in capsules and well below the RDA - as such, no ingredient is given in a medicinal dose. Because the doses are all below RDA, safety issues for any of the proposed ingredients are very unlikely. Further, all doses are well below the Tolerable Upper Intake Limit (UL), which is considered the highest amount of daily nutrient intake that is not likely to cause any adverse effects (Nutritional Institutes of Health, n.d.). This low risk of adverse effects was supported by the findings of the STAR trial (not published), showing that only a small number of side effects were present in the study (drowsiness and reduced appetite), and these were temporary and disappeared during the duration of the trial.

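### Hypothesis 8 predicts a finding of safety, but 40 children can only describe common side effects: with no serious or lasting event in 40, true rates up to 7.2% (one-sided) or 8.8% (two-sided) remain possible

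*Protocol*

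**What the plan says.** The eighth of nine items under Hypotheses in the protocol predicts that the product "will be found to be a safe intervention that has a low incidence of side effects which will be mild in severity and only last" briefly, and that families will be satisfied. It gives no rate that would count as low and no criterion for *safe*.

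Under Participant recruitment (Sample size), the protocol states: "Forty participants will be sought for the study, split 20:20 between group 1 and 2". The reasons given are that this number suffices to show whether the sticks "are successful in reducing emotion dysregulation with sufficient power" and that it allows enough replications for a single-case design. No safety reason is given.

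Under Study design, both groups eventually take the product. Group 1 has 4 weeks on and later 12 more. Group 2 has a delayed 4 weeks on, after which "Group 2 starts taking the multinutrient intervention for another 12 weeks". All 40 children are therefore meant to be exposed, for up to 4 + 12 = 16 weeks each.

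On what is collected, Assessment Tools says "Side effects will be assessed every two weeks", using an adapted checklist listed among the secondary measures. The safety protocol adds: "Serious adverse events would include events that result in hospitalisation, life-threatening disability or death". Statistical Analysis describes no analysis of side effects or adverse events; its only stated confidence interval is for Cohen's *d*.

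**The concern.** Hypothesis 8 combines two kinds of statement. One describes the side effects that will be seen: how many, how severe, how long. The other is a verdict on the product, that it will be found safe. The first can be checked in 40 children. The second depends on events that may be too rare to appear in 40 children, so a clean record says little about them.

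The mismatch lies in the protocol itself, because the protocol fixes both the verdict hoped for and the sample size. If no serious or lasting event occurs and the hypothesis is reported as confirmed in its own words, readers would be told that a daily supplement is safe in 5 to 10 year-olds. The data would still be compatible with such events in several percent of them.

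**Working it through.** **Inputs.** The number exposed is 40, from Sample size and Study design. The protocol foresees discontinuation and withdrawal but gives no rate, so 40 is the best case; 30 exposed is used below as an assumed lower value. No expected rate for any event class is given, so the rates used are assumptions. Events are taken as independent between children. The protocol attaches no confidence level to event rates, so 95% is assumed.

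**The plan's own figure.** There is no safety figure to reproduce. The protocol states no target rate, precision or bound, and the basis given for 40 concerns efficacy and replication.

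**Step 1: what zero events would exclude.** With no event in *n* children, the exact upper limit is 1 − 0.05^(1/*n*) (one-sided 95%) or 1 − 0.025^(1/*n*) (two-sided 95%).

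| Children exposed | One-sided 95% | Two-sided 95% |
|---|---|---|
| 40 | 1 − 0.05^(1/40) = 7.2% | 1 − 0.025^(1/40) = 8.8% |
| 30 (assumed) | 1 − 0.05^(1/30) = 9.5% | 1 − 0.025^(1/30) = 11.6% |

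These limits depend on the number exposed and the confidence level, and on no assumed event rate.

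**Step 2: how often a real problem would go unseen (illustration).** The chance of seeing no event in 40 is (1 − *p*)^40.

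| Assumed true rate | Chance of no event in 40 |
|---|---|
| 1% | 0.99^40 = 67% |
| 2% | 0.98^40 = 45% |
| 3% | 0.97^40 = 30% |
| 5% | 0.95^40 = 13% |

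With 30 exposed, the figure at 2% is 0.98^30 = 54.5%. For scale, a 95% chance of seeing at least one event at a true rate of 2% needs ln 0.05 / ln 0.98 = 148.3, so 149 exposed children.

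**Step 3: what 40 children can show.** At a true incidence of 10%, the chance of seeing no case is 0.90^40 = 1.5%. At 20% it is 0.80^40, about 0.01%. A side effect that common would almost certainly appear.

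**The case against.** Four arguments weigh against a stronger criticism, and most of each stands.

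*Hypothesis 8 is a prediction, not a decision rule.* A reader might infer that the trial will declare the product safe as soon as no serious event is seen. No section says so. The hypothesis names observable features and does not mention zero events. What remains is that it makes safety something the trial is to find.

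*Ceilings and intervals belong in the statistical analysis plan.* A reader might treat their absence from the protocol as the defect. It is not, since a plan may exist that is not shown. But an interval added there would not make 40 children support an unqualified statement of safety.

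*The assumed rates have no source.* A reader might infer that a serious reaction in 1 in 50 children is expected. Nothing supports that. The protocol reports doses below the recommended daily amount and the upper limit, and no serious side effects in 34 earlier studies of the formula. The 1% to 5% rates are therefore illustrative. The low-dose argument and the earlier studies are reasons to expect safety, however, and not something this trial would find. The earlier trial of this delivery form was unpublished and in university students.

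*Safety is not the main question.* The stated aim is feasibility and effectiveness in an explorative study, and serious events have separate review and reporting. So it would be wrong to say that a main hypothesis fails, or that the trial is uninformative about side effects; Step 3 shows that it is informative about common ones.

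**Conclusion.** The concern holds in limited form. Forty children can support a description of common side effects. They cannot establish safety for serious, non-mild or lasting events: if none occurs, true rates up to 7.2% (one-sided 95%) or 8.8% (two-sided 95%) are not excluded. This assumes that all 40 are exposed and that events are independent; with fewer exposed, the limits rise. The gap is between one word in Hypothesis 8 and a sample size chosen for other reasons. It affects how the safety result is worded and leaves the efficacy analysis untouched.

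**What to change.** 1. Restate Hypothesis 8 as a tolerability hypothesis about the incidence, severity and duration of the side effects observed, and drop the prediction that the product will be found safe.
2. For serious events, events not rated mild, and events that persist, report the number of children affected with the exact (Clopper-Pearson) 95% limits. Use the number of children actually exposed as the denominator, not the number enrolled.
3. Word the conclusion by the limit. For example, if none of 40 exposed children has a serious event, say that rates above about 9% are excluded (two-sided 95%) and that lower rates are not.

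Because these counts depend on the side-effect data, the protocol should also reconcile its two statements on how often safety is assessed (every two weeks under Assessment Tools, once a month in the safety protocol) and the absence of the checklist from the schedule in Appendix B.

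The cost is a few sentences and one exact interval per event class, with no further children. The drawback is a less favourable safety statement.
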